**Figure 2. f2:**
[figure not shown]
Schematic to describe second randomisation to intravenous rifampicin (IV RIF). All consenting LASER-TBM participants in experimental arms (n = 60) will undergo a second randomisation to receive either oral (35mg/kg) or IV (20mg/kg) RIF, together with linezolid (LZD) (with or without aspirin), at the time of study entry. The second randomisation will take place at the time of study entry, prior to receipt of study drug. Randomisation will be done in a 1:1 ratio using an electronic randomization tool, and fully integrated with main trial procedures). Due to the nature of the intervention, and because the outcome measure is a pharmacokinetic (PK) endpoint, allocation of IV versus oral RIF will be unblinded. Study drug will be stored at site pharmacies and administered as an infusion, in accordance with instructions in the package insert and trial standard operating procedures (SOP), by nursing staff of the trial.

There are six scheduled study visits, which will occur at study sites or affiliated stepdown facilities. Visits will involve clinical history, examination, phlebotomy, lumbar puncture and brain imaging at the timepoints shown in
Figure 1. In those who consent, intensive PK sampling will take place at day 3 (see
Figure 3). Trial participation will be for 180 days post-randomisation: primary safety endpoints and secondary efficacy endpoints will be evaluated at day 56; additional secondary endpoints will be evaluated at day 180 through record review.

**Figure 3. f3:**
[figure not shown]
Schematic to summarise intensive pharmacokinetic (PK) sampling schedule. All participants (n=100) will be offered participation in the intensive sampling component of the PK sub-study at the time of randomization to the main study. Intensive plasma sampling will take place at the Day 3 study visit. Serial venous blood samples will be collected through a peripheral intravenous catheter pre-dose, and at 0.5, 1, 2, 3, 6, 8 - 10, and 24 hours after witnessed drug intake and an overnight fast. Sparse sampling will be performed at Day 3 for participants who decline intensive sampling or in whom this fails.

**The primary endpoint of the study is:** The incidence of solicited treatment-related AE (see
Table 1) and death at 56 days associated with increased dose RIF plus LZD with or without adjunctive ASA, when administered alongside standard antitubercular therapy.

**Table 1. T1:** Solicited treatment related adverse events, objective measures for assessment and management plan in each setting. Grade relates to Division of AIDS (DAIDS) criteria
^
37
^. ASA, Asprin; RIF, Rifampicin; LZD, Linezolid.

Adverse Event (responsible study drug)	Objective measure	Parameter	Management
Gastrointestinal haemorrhage (ASA)	Clinical and laboratory measures suggesting GI haemorrhage.	i) Vomiting fresh or changed blood of any volume, ii) Melena, iii) Unexplained drop in Hb concentration of >2g/L or iv) > 5mls of fresh or changed blood aspirated from nasogastric tube.	Discontinue study drug permanently.
Intracerebral haemorrhage (ASA)	Radiological evidence of haemorrhage.	CT or MRI finding	Discontinue study drug permanently.
Transaminitis (RIF)	alanine tranferase (ALT), bilirubin	New Grade 3 or above	Discontinue study drug (and other potentially hepatotoxic agents). Place on alternative treatment for TBM if background regimen affected. Re-test every 2 days. Resume study drug with an escalating dose rechallenge once ALT < 100 IU and total bilirubin within normal range.
Anaemia (LZD)	Hemoglobin (Hb)	New Grade 3	Discontinue study drug (plus any other myelosuppressive drugs as appropriate). Consider transfusion with packed cells or erythropoietin therapy. Monitor Hb twice weekly. Restart at 50% dose once Hb ≥ 8 mg/dL
		New Grade 4	Discontinue study drug permanently. Consider hospital admission and/or transfusion with packed cells or erythropoietin therapy. Re-test every 2 days.
Neutropenia (LZD)	Neutrophils	New Grade 3	Discontinue study drug. Monitor white cell count (WCC) every week. Restart at 50% dose once neutrophil count 0.5 x 109 cells/L.
		New Grade 4	Discontinue study drug permanently. Consider therapy with GM-CSF. Monitor WCC every 1 – 2 days.
Thrombocytopenia (LZD)	Platelet (Plt) count	New Grade 3	Discontinue study drug (plus any other myelosuppressive drugs as appropriate). Monitor Plt count twice weekly. Restart at 50% dose once Plt count > 50 x109 cells/L.
		New Grade 4	Discontinue study drug permanently. Consider hospital admission and/or transfusion pooled Plts. Re-test every 1 - 2 days.
Peripheral Neuropathy (LZD)	Full neurological history and examination, Brief Peripheral Neuropathy Score (BPNS) and Modified Total Neuropathy Score (mTNS)	Change in clinical history of examination resulting in: I) 1 grade increase in BPNS ii) 2 grade change in any modality on mTNS	Review with a view to discontinuing study drug (plus any other neuropathic drugs like INH). Consider restarting at 50% dose once completely resolved.
Optic Neuropathy (LZD)	14-plate Ishihara Test, visual acuity measured by logMAR chart	Change in score of 2 on 14-plate Ishihara Colour Test or new or worse logMAR score of 0.2	Stop study drug and EMB and refer for formal ophthalmological assessment. If assessment consistent with optic neuritis do not restart drug.

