**Figure 1. f1:**
[figure not shown]
Study design schematic describing randomisation to study arms, treatment intervention per am, visit schedule, overview of clinical procedures and timepoints relating to primary and secondary endpoint data collection. RHZE: Rifampicin, Isoniazid, Pyrazinamide, Ethambutol; R
_10_: Rifampicin 10mg/kg/day; R
_35_: Rifampicin 35mg/kg/day; LZD: Linezolid; ASA; Aspirin.

Treatment will be provided in all arms for 56 days, after which participants will be referred back to public sector facilities to complete standard therapy for HIV-associated TBM. All participants will receive antitubercular chemotherapy as well as corticosteroids as per standard practice. Participants allocated to experimental arms 2 and 3 will receive additional RIF (total oral dose 35 mg/kg/day once daily) for 56 days plus oral LZD 1200mg once daily for the first 28 days, reduced to 600 mg daily for the next 28 days. Those randomised to experimental arm 3 will also receive oral aspirin 1000 mg once daily for 56 days. A second randomization will take place before receipt of study drug for participants in the experimental arms (n = 60) to receive either oral (35 mg/kg) or intravenous (20 mg/kg) RIF (see
Figure 2). This will be continued for 3 days, after which all participants will receive oral RIF for the remainder of the intervention period (53 days). 

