**Secondary study endpoints are:**

• Death and severe disability (Modified Rankin Scale Grade 5) at 56 days (
Box 1).

**Table T5:** Box 1. Modified Rankin score

**SCORE**	**DESCRIPTION**
0	No symptoms
1	No significant disability. Able to carry out usual activities, despite some symptoms.
2	Slight disability. Able to look after own affairs without assistance, but unable to carry out all previous activities.
3	Moderate disability. Requires some help, but able to walk unassisted.
4	Moderately severe disability. Unable to attend to own bodily needs without assistance, and unable to walk unassisted.
5	Severe disability. Requires constant nursing care and attention, bedridden, incontinent.
6	Dead

• Death at 56 and 180 days.

• Disability at 56 and 180 days, stratified by baseline MRC grade.

• Grade 3 or 4 AE.

• Permanent discontinuation of experimental drugs.

• Severity and frequency of haematologic and neurologic AE related to LZD use.

• Severity and frequency of major bleeding (gastrointestinal and intracerebral) related to ASA use.

•
*M. tb* culture status and time to positivity in automated liquid culture (MGIT) and Gene Xpert® Ultra cycle threshold (C
_t_) values at days 28 and 56.

• The occurrence of TBM-IRIS assessed by the modified International Network for the Study of HIV-associated IRIS (INSHI) criteria
^
35
^.

• MRI and CT changes at day 56.

Study participants for LASER TBM must be adults (aged 18 years or over), with proven HIV-1 seropositivity, and a diagnosis of TBM meeting criteria for ‘possible’, ‘probable’ or ‘definite’ as per the published consensus definition
^
36
^.

Potential participants will be excluded if they meet any of the exclusion criteria outlined in
Box 2.

Box 2. Eligibility criteria

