**Exclusion criteria**
•   Rifampicin-resistant
*M.tb* detected on any clinical specimen;•   History of allergy or hypersensitivity to RIF, isoniazid, ethambutol, pyrazinamide, LZD or ASA;•   Received more than 5 days of antitubercular therapy in the 30 days prior to screening;•   Receipt of regular daily ASA or NSAID prior to TBM diagnosis•   CSF unobtainable by lumbar puncture or another procedure;•   Evidence of bacterial or cryptococcal meningitis;•   Severe concurrent uncontrolled opportunistic infection including, but not limited to, active cytomegalovirus-associated disease, Kaposi sarcoma,
*Pneumocystis jirovecii* pneumonia, HIV related or unrelated malignancy, or gastrointestinal bleeding;•   Any other form of immunosuppressive therapy, including antineoplastic and biologic agents, apart from corticosteroids;•   More than 17 weeks pregnant at baseline;•   Peripheral neuropathy scoring Grade 3 or above on the BPNS;•   Any disease or condition in which the use of the standard anti-TB drugs (or any of their components) are contraindicated. This includes, but is not limited to, allergy to any TB drug or their components;•   The presence of one or more of the following:-   Estimated glomerular filtration rate (eGFR) < 20ml/min/1.73 m2
*
-   INR > 1.4 and/or clinical evidence of liver failure or decompensated cirrhosis;-   Haemoglobin < 8.0 g/dL;-   Platelets < 50 x109 /L;-   Neutrophils < 0.5 x 109 cells/L;•   Any disease or condition in which any of the medicinal products listed in the section pertaining to prohibited medication (See
Box 1) is used and cannot be safely stopped;•   Known or suspected history of drug abuse or any other reason that is, in the opinion of investigators, sufficient to compromise the safety or cooperation of the participant.*Calculated using the Cockcroft-Gault equation; INR: International normalised ration; BPNS: Brief peripheral neuropathy score; NSAID: Non-steroidal anti-inflammatory drug.

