## Recruitment, randomisation, retention and withdrawal

Recruitment will be from inpatients at the participating hospital sites in South Africa (Groote Schuur Hospital, Mitchells Plain Hospital, New Somerset Hospital and Livingstone Hospital). Suitable patients will be identified by attending ward doctors and co-investigators at each site and referred to the study staff for screening.

Participant identification numbers (PID), assigned at the screening visit, will be used throughout the study. After signing the informed consent document, eligible participants will be randomised to one of the treatment arms using a pre-generated electronic randomisation list created within Microsoft Excel prior to commencement of the study. The randomisation list will be generated and updated by the trial pharmacist who will have no direct contact with trial participants or involvement with the assessment for eligibility in the trial. The second randomisation to IV or oral RIF will take place immediately, prior to receipt of study drug, for all participants allocated to experimental arms. The trial is open-label, and regimens will not be masked therefore all study team members involved in the participants care will be aware of the study arm allocation.

All trial procedures will take place in hospital during the admission period. The decision to discharge trial participants will be made by clinical, and not trial, staff. Site-specific standard operation procedures (SOP) will be developed for trial follow up visits following discharge or referral to a stepdown facility. 

A participant will be withdrawn from the study if:

• The initial
*M.tb* strain is found to be RIF-resistant on confirmatory testing;

• HIV-1 result is found to be negative on confirmatory testing;

• An alternative diagnosis is established within 5 days of antitubercular treatment initiation which leads the treating physician to discontinue antitubercular therapy;

• Withdrawal of informed consent.

Participants who withdraw consent prior to completion of the study will not undergo any further study procedures or data collection. In such cases, consent for the use of data collected prior to withdrawal of consent will be sought from the withdrawing participants. There will be no replacement for participants withdrawn from the trial.

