### Solicited treatment related AE

Table 1 lists AE of special interest which are considered ‘solicited treatment related AE’ and therefore comprise primary safety endpoints of this study. These AE are reported regardless of causal relationship to study drugs. For each AE there is a specific objective measure incorporating the DAIDS grading criteria and other parameters of clinical significance. The management of each AE is summarised.

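### Table 1 misprints two haemoglobin units: the GI-haemorrhage trigger in the primary endpoint (2 g/L, which is 0.2 g/dL) and the linezolid restart level (8 mg/dL)

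*Protocol article*

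**What the plan says.** Table 1 lists the solicited treatment-related adverse events, the parameter that defines each, and its management.

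- **Gastrointestinal haemorrhage (aspirin).** Four alternative criteria are joined by *or*. The third is "Unexplained drop in Hb concentration of >2g/L". Management is "Discontinue study drug permanently".
- **Anaemia (linezolid), new Grade 3.** Linezolid is interrupted, then "Restart at 50% dose once Hb ≥ 8 mg/dL".

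The only other haemoglobin threshold in the article is the exclusion criterion in Box 2, "Haemoglobin < 8.0 g/dL".

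Table 1 events plus death at 56 days form the primary endpoint. Under *Solicited treatment related AE*, causality does not filter them: "These AE are reported regardless of causal relationship to study drugs". Under *Safety oversight*, the DSMB may advise pausing or stopping enrolment on the frequency and severity of these same events.

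**The concern.** A fall of 0.2 g/dL lies within ordinary variation between two haemoglobin measurements, so it cannot sensibly define a haemorrhage that ends a drug for good. It also sits oddly within Table 1, where anaemia itself counts only from a new Grade 3. The restart level of 8 mg/dL is physically meaningless: as printed, the condition is always met.

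The first error matters more because it is part of the primary endpoint. Used literally, it could count participants with stable haemoglobin as bleeding cases in all three arms. The one check in the criterion itself is that the drop be unexplained, and that judgement is made by staff who know the allocation: "The trial is open-label, and regimens will not be masked".

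- If staff judge alike in all arms, the false events dilute a real difference between arms and can mask harm.
- If staff judge differently by arm, the false events create or distort a difference.

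The permanent stop falls chiefly on the aspirin arm, about 30 of the 100 participants: "Those randomised to experimental arm 3 will also receive oral aspirin 1000 mg once daily for 56 days". The secondary endpoint "Severity and frequency of major bleeding (gastrointestinal and intracerebral) related to ASA use" may be affected too, but the article does not say that the Table 1 trigger defines major bleeding.

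**Working it through.** **Unit conversion** (1 g/dL = 10 g/L = 1000 mg/dL)

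- Trigger: 2 g/L = 0.2 g/dL. Against the Box 2 limit, 0.2 / 8.0 = 2.5%. A trigger of 2 g/dL is 20 g/L, ten times the printed value.
- Restart level: 8 mg/dL = 0.008 g/dL. The Box 2 limit of 8.0 g/dL is 1000 times larger.

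**How often chance alone meets the trigger**

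Assumptions not in the article: within-person SD of 2 to 5 g/L, drop measured from baseline, one follow-up value per participant, both values independent and normal, no true change. Then

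P(drop > c) = 1 − Φ( c / (SD × √2) ).

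| SD (g/L) | c = 2 g/L | c = 20 g/L (2 g/dL) |
|---|---|---|
| 2 | 0.240 | 7.7 × 10⁻¹³ |
| 3 | 0.319 | 1.2 × 10⁻⁶ |
| 4 | 0.362 | 0.0002 |
| 5 | 0.389 | 0.0023 |

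Worked line, SD 2: 2 / (2 × 1.414) = 0.707, and 1 − Φ(0.707) = 0.240.

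No figure is given for repeated testing, because the full-blood-count row of Table 4 carries no visit marks in the text available.

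**False events in the endpoint**

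Let k be the share of such drops that staff accept as unexplained bleeding (assumed). The false-event rate is q = k × P.

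- k = 0.25: q = 0.060 to 0.097
- k = 0.5: q = 0.120 to 0.194
- k = 1 (qualifier ignored): q = 0.240 to 0.389

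**Equal judgement in all arms.** If false events are independent of true ones, the observed risk is p + (1 − p)q, so the observed difference is (1 − q) × the true difference. The sample size section's scenario of 10/20 against 14/20 is a 20-point difference. It becomes:

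- k = 0.25: 18.8 to 18.1 points
- k = 0.5: 17.6 to 16.1 points
- k = 1: 15.2 to 12.2 points

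**Unequal judgement.** Take no true difference, a 50% base rate, k = 0.1 in control and k = 0.5 in the aspirin arm.

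- SD 2: 0.512 against 0.560, a spurious 4.8 points
- SD 5: 0.519 against 0.597, a spurious 7.8 points

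**Permanent aspirin stops.** With n = 30, 30 × q runs from 1.8 (k = 0.25, SD 2) to 5.8 (k = 0.5, SD 5), so about 2 to 6 participants.

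**The case against.** The strongest reply is that nobody would apply these values. The haemorrhage row also has an objective-measure column asking for clinical and laboratory measures that suggest GI bleeding, and a clinician would hardly read a 2 g/L change in a stable patient that way. Detailed guidance on managing adverse events sits in an operating manual that is not shown, and the article condenses protocol V6. Either may carry the right units.

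Much of this stands as a limit on impact:

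- Nothing shows that sites used 0.2 g/dL, and the k = 1 figures are ceilings.
- The SD and acceptance rates are assumptions. With an SD of 7 g/L, chance drops would be 42% at 2 g/L and about 2% at 2 g/dL, so the 0.23% holds only up to an SD of 5 g/L.
- The two errors are not equally certain. The mg/dL value is impossible. The g/L value is a valid unit, so that error is inferred, and the article never states 2 g/dL.
- The restart level is a management rule outside the endpoint definition.
- The missing reference value for the drop is a detail that an article may leave to the full protocol.

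It does not remove the error. The parameter column sets the operational cut-off, the criteria are alternatives, and a correct unit in an unseen manual would not repair a wrong definition in the published endpoint table.

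**Conclusion.** The point holds. Table 1 prints two wrong haemoglobin units: one is a component of the primary endpoint, very probably ten times too small, and the other is a restart rule 1000 times too small. The conversions need no assumption.

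The size of any effect is conditional on literal use. At a within-person SD of 2 to 5 g/L and 25% to 50% acceptance as unexplained, 6% to 19% of stable participants would become false events. The general conclusion does not hinge on the exact SD: at the printed trigger measurement noise qualifies often, and at 2 g/dL it rarely does.

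This should be corrected without delay, because the definition feeds the primary comparison, the DSMB's reviews after every 15 participants, and a permanent drug stop.

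**What to change.** Subject to confirmation by the sponsor's clinical lead:

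1. Change the haemorrhage trigger to an unexplained fall in haemoglobin of >2 g/dL, and, since the row is being edited, name the reference value (for example baseline).
2. Change the linezolid restart level to haemoglobin ≥ 8 g/dL, which matches the Box 2 limit.
3. Check which units protocol V6 and the operating manual carry, and notify sites and the DSMB.
4. As a precaution, re-check GI-haemorrhage events in all arms and aspirin discontinuations in arm 3 already coded among the 52 participants enrolled.

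The cost is two unit corrections, one reference value, a short note and a brief re-check. Sample size, analysis methods and visit schedule are unaffected.

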**Secondary study endpoints are:**

• Death and severe disability (Modified Rankin Scale Grade 5) at 56 days (
Box 1).

**Table T5:** Box 1. Modified Rankin score

**SCORE**	**DESCRIPTION**
0	No symptoms
1	No significant disability. Able to carry out usual activities, despite some symptoms.
2	Slight disability. Able to look after own affairs without assistance, but unable to carry out all previous activities.
3	Moderate disability. Requires some help, but able to walk unassisted.
4	Moderately severe disability. Unable to attend to own bodily needs without assistance, and unable to walk unassisted.
5	Severe disability. Requires constant nursing care and attention, bedridden, incontinent.
6	Dead

• Death at 56 and 180 days.

• Disability at 56 and 180 days, stratified by baseline MRC grade.

• Grade 3 or 4 AE.

• Permanent discontinuation of experimental drugs.

• Severity and frequency of haematologic and neurologic AE related to LZD use.

• Severity and frequency of major bleeding (gastrointestinal and intracerebral) related to ASA use.

•
*M. tb* culture status and time to positivity in automated liquid culture (MGIT) and Gene Xpert® Ultra cycle threshold (C
_t_) values at days 28 and 56.

• The occurrence of TBM-IRIS assessed by the modified International Network for the Study of HIV-associated IRIS (INSHI) criteria
^
35
^.

• MRI and CT changes at day 56.

Study participants for LASER TBM must be adults (aged 18 years or over), with proven HIV-1 seropositivity, and a diagnosis of TBM meeting criteria for ‘possible’, ‘probable’ or ‘definite’ as per the published consensus definition
^
36
^.

Potential participants will be excluded if they meet any of the exclusion criteria outlined in
Box 2.

Box 2. Eligibility criteria

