## Statistical considerations

### Sample size

The total number of participants required for primary safety analysis is 100. This encompasses:

Arm 1 - control - (standard-of-care): 40

Arm 2 - experimental - (standard-of care + high dose rifampicin + linezolid): 30

Arm 3 - experimental - (standard-of care + high dose rifampicin + linezolid + aspirin): 30

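### Two secondary safety endpoints are worded by relation to linezolid or aspirin, so on a literal reading the arms that do not receive the drug have no countable events

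*Protocol article*

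**What the plan says.** The list of secondary endpoints in the protocol article contains two items tied to a drug: "Severity and frequency of haematologic and neurologic AE related to LZD use" and "Severity and frequency of major bleeding (gastrointestinal and intracerebral) related to ASA use". A third item, "Permanent discontinuation of experimental drugs", names the drugs but contains no wording about relatedness.

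The Sample size section gives the arms as "Arm 1 - control - (standard-of-care): 40", "Arm 2 - experimental - (standard-of care + high dose rifampicin + linezolid): 30" and "Arm 3 - experimental - (standard-of care + high dose rifampicin + linezolid + aspirin): 30". Table 2 confirms that linezolid is given in arms 2 and 3 only, and aspirin in arm 3 only.

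For the solicited events of Table 1, which make up the primary endpoint together with death, the section on solicited events sets a different rule: "These AE are reported regardless of causal relationship to study drugs". The trial is open-label, and the section on recruitment and randomisation says that "all study team members involved in the participants care will be aware of the study arm allocation".

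**The concern.** An event in a participant who never took linezolid cannot, in the ordinary sense of the words, be related to linezolid. The same holds for bleeding and aspirin in arms 1 and 2. If the endpoints are applied that way, the comparator count is zero whatever happened to those participants. The count in the treated arms becomes the number of events that someone, knowing the allocation, ascribed to the drug.

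The background rate is unlikely to be zero. The management column of Table 1 names isoniazid as another cause to consider in neuropathy, stops ethambutol together with study drug in optic neuropathy, and refers to other myelosuppressive drugs. Isoniazid and ethambutol are given in every arm (Table 2).

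At stake is the drug-specific safety information for the planned phase III trial. The primary endpoint pools all solicited events with death, and the grade 3 or 4 endpoint pools every type of adverse event. Neither isolates linezolid toxicity or aspirin bleeding; among the listed endpoints, only these two do.

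**Working it through.** The article states no rate, power or test for these endpoints, so there is no figure to reproduce. The check has two parts.

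**1. What can be counted under each reading**

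| Endpoint | Reading | Arm 1 (n=40) | Arm 2 (n=30) | Arm 3 (n=30) |
|---|---|---|---|---|
| Linezolid | literal | 0/40 always | attributed events | attributed events |
| Linezolid | event type, any cause | all events | all events | all events |
| Aspirin | literal | 0/40 always | 0/30 always | attributed events |
| Aspirin | event type, any cause | all events | all events | all events |

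The article does not say which reading applies. Two analysts with the same data could report different control-arm counts.

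**2. How much the choice could matter, if arms were compared**

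Inputs: 40 controls and 30 in one experimental arm (Sample size section). The background rate b, the true excess d and the share of events attributed are assumptions, because the article gives none of them.

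*Size of the difference.* The true risk difference is (b + d) − b = d. On the literal reading the control rate is 0, and the experimental rate runs from d (only true drug effects attributed) to b + d (everything attributed).
- b = 10%, d = 10 points: the reported difference is 10 to 20 points.
- b = 20%, d = 10 points: the reported difference is 10 to 30 points.
- Under-attribution could take it below 10 points.

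*Spurious significance when d = 0.* With 0/40 in control, the Fisher p-values are:
- 3/30: C(30,3)/C(70,3) = 4,060/54,740 = 0.074.
- 4/30: C(30,4)/C(70,4) = 27,405/916,895 = 0.030.

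These are two-sided, since every other table with the same margins is more probable. Four attributed events are therefore enough for p<0.05. On the literal reading the chance of this is P(X ≥ 4) with X ~ Binomial(30, q), where q is b times the share attributed. For all-cause counting, both binomials are enumerated and the Fisher p-value is computed for each table.

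| Assumed background rate, same in both arms | Literal, all attributed | Literal, half attributed | All-cause in both arms |
|---|---|---|---|
| 5% | 6.1% | 0.6% | 1.2% |
| 10% | 35.3% | 6.1% | 2.7% |
| 20% | 87.7% | 35.3% | 3.6% |
| 30% | 99.1% | 67.8% | 3.8% |

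The inflation comes from the fixed zero and from over-attribution. With no over-attribution, the literal count is not biased upward.

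**The case against.** The strongest reply is that the article's own usage points the other way. Table 1 assigns a responsible drug to each type of event as a fixed label: cytopenias and neuropathies to linezolid, gastrointestinal and intracerebral haemorrhage to aspirin. These events are called treatment-related in their title and are still reported whatever their cause. The two secondary endpoints pair the same kinds of event with the same drugs. If the phrase means only the Table 1 label, control events count and there is no structural zero. The article also describes no causality judgement feeding these endpoints, and it leaves secondary analyses to a separate analysis plan.

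This stands in part. It shows that the literal reading is a reading and not a stated rule. It does not settle the matter. The any-cause rule is stated for the solicited events that form the primary endpoint, and the two secondary items do not refer to Table 1. Nor do they match it exactly: they speak of major bleeding and of severity, whereas Table 1 accepts vomited blood of any volume and, for the cytopenias, only new grade 3 or 4 events. What an endpoint counts is part of its definition and is not a detail of its analysis.

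A reader might go further and infer that three endpoints are affected, that controls score zero by rule, and that background toxicity is booked to the experimental drugs. The documents do not support this. The discontinuation item contains no attribution wording and is a legitimate tolerability measure in those who take the drugs. Rifampicin is given in arm 1 as well, at the standard dose, so it is not a drug that controls never receive. No counting rule and no between-arm comparison is stated for the two remaining endpoints.

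**Conclusion.** The point holds for two endpoints and as a defect of definition. Read literally, the linezolid endpoint has no comparator count in arm 1, the aspirin endpoint has none in arms 1 and 2, and the remaining counts rest on unmasked attribution.

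The size is illustrative. The figure of 35% to 88% spurious significance needs an assumed background rate of 10% to 20%, attribution of every event, and a Fisher test that the article does not state for these endpoints. Half attribution gives 6% to 35%, and all-cause counting under 4%. Even without a test, a table that sets a structural zero beside a treated-arm count would mislead.

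It would be wrong to infer that the randomised safety comparison is lost. The primary endpoint counts solicited events and deaths in every arm and compares each experimental arm with control, and the grade 3 or 4 endpoint carries no attribution. No stated figure changes and the primary safety conclusion is unaffected. The wording should still be corrected, because no other listed endpoint isolates these toxicities.

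**What to change.** In the list of secondary endpoints, state that both items count the named types of event (haematologic and neurologic adverse events; major gastrointestinal and intracerebral bleeding) in all three arms regardless of attribution, following the rule already set for the solicited events. Give investigator attribution, if recorded, only as supplementary description.

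Keep the discontinuation endpoint as it is, and label it as descriptive within the arms that receive those drugs.

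The cost is low but not nil. Adverse events are already assessed and graded at all scheduled visits in all participants, so the change calls for no new assessments. With 52 participants enrolled, it does need a formal amendment under the article's amendment policy, and the tables become slightly longer.
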